#### Clinical characteristics.

Blood pressure and blood parameters are collected. In the latter, the levels of glucose, glycosylated hemoglobin (HbA1c), homeostasis model assessment-insulin residence (HOMA-IR), total cholesterol, high-density lipoprotein cholesterol (HDL-c), low-density lipoprotein cholesterol (LDL-c), triglycerides (TG), aspartate aminotransferase (AST), alanine aminotransferase (ALT) and gamma-glutamyl transferase (GAG) are examined, triglycerides (TG), aspartate aminotransferase (AST), alanine aminotransferase (ALT) and gamma-glutamyl transferase (GGT), creatinine, urea, creatinine clearance, iron, ferritin, sodium, potassium and C-reactive protein (CRP).

Blood samples will be drawn after a fasting period of at least 8 hours (no food or beverage intake) at the corresponding health center. Handling and transport will be conducted in accordance with standardized quality protocols, and the samples will be processed and analyzed in an accredited laboratory, following the current regulations of the Community of La Rioja. Biochemical analyses will be performed using automated techniques, employing equipment that is periodically calibrated and validated.

In relation to blood pressure, measurements will be taken at the corresponding health center. Readings will be obtained over the brachial artery, after 5 minutes of rest while seated and with the arms resting at heart level. Long-sleeved shirts will be removed for a correct reading and the cuff size must be adequate.

Data related to diabetes disease (year of diagnosis, antidiabetic treatment currently used, associated complications and frequency of Health care), smoking, alcohol consumption, past injuries and major surgeries, sedentary lifestyle, motivation to change physical exercise, physical activity and quality of life will also be collected through medical history and self-report.

#### Level of sedentary lifestyle.

The level of sedentary lifestyle will be measured with the use of accelerometers and a questionnaire validated in Spanish. The questionnaire used is the Spanish version of the SBQ (S4 Appendix). This instrument measures the time spent in sedentary behaviors from the time the person gets up to the time he/she goes to bed, both during the week and at weekends. The responses are provided on numerical scales, and then the total number of hours spent on each activity is summed. The interclass correlation is 0.83–0.86 and the reliability index of the questions varies from 0.52 to 0.96 [32].

In addition, sedentary time will be evaluated quantitatively using accelerometers. The model used in our study is the ActiTrainer, which is small (8.56 x 3.81 x 1.52 cm) and light (48 g), ensuring great comfort during use. Previous studies have supported its use for an objective and more reliable measurement of the effectiveness of interventions [33–38] They will be placed by the study nurse during the measurement periods (T0-3), however, both the participants of the CG and the IG will receive training on their proper placement, removal and protocol. These should be worn at the waist, fastened with a well-fitting elastic belt, placed in the morning and removed at bedtime and during periods of exposure to water (bath, shower, swimming, etc.). To avoid skin irritation in case of incorrect fit, they may be worn over clothing. Participants must wear the device for 5 consecutive days, with a minimum of 10 waking hours per day.

This device only detects human movement, electronically filtering high-frequency vibrations produced by cars, buses, trains, etc. It has no other function than to measure physical activity through an encryption of internal operations that require specific software and cannot be used for any other purpose. It does not emit radiation or interfere with the human body. However, any eventuality must be reported.

Sedentary behavior will be defined as any period with ≤100 counts per minute (cpm) recorded by the ActiTrainer accelerometer. This threshold has been widely accepted in the scientific literature and specifically validated in adults against reference systems such as the IDEEA monitor, considered an almost gold standard for postural measurement, showing good agreement in estimated sedentary time [39]. Additionally, the cut-off points established by Freedson et al. (1998) will be used to classify physical activity as light (101–1951 cpm), moderate (1952–5724 cpm), vigorous (5725–9498 cpm), and very vigorous (>9498 cpm), according to estimated energy expenditure in METs [40].

For the processing of the collected data, only days with a minimum of 10 hours of device wear time during waking hours will be considered valid. A minimum of 4 valid days, including at least one weekend day, will be required for the record to be deemed representative, in accordance with criteria established in previous studies [39,41]. Periods of non-wear, due to non-compliance or technical issues, will be excluded from the analysis based on validated algorithms for non-wear time detection, which automatically identify intervals of consecutive zero activity counts exceeding 60 minutes [42]. Should any participant fail to meet the minimum valid day criteria, a sensitivity analysis will be conducted, and the number of valid days per participant will be reported to ensure transparency and data quality.

#### State of motivation to change.

Measured by the TMPEC questionnaire (S5 Appendix). This questionnaire aims to identify which stage of the transtheoretical model of change a person is in regarding his or her willingness to engage in physical exercise. The stages of change include precontemplation, contemplation, preparation, action, maintenance, and relapse. The questionnaire has items that use a respond scale from 1 (strongly disagree) to 5 (strongly agree) of reasons for not exercising, these items should only be completed by participants who do not exercise regularly. Similar items are rated in the table with the reasons why the participants perform physical exercise on a regular basis, the answers are rated on the same Likert-type scale from 1 to 5. The measurement of the questionnaire is performed by analyzing the average score of each corresponding stage of the transtheoretical model of change. Higher scores on each subscale of the questionnaire reflect a greater identification with the corresponding stage of behavioral change. Specifically, mean scores equal to or greater than 4 indicate a strong identification with that stage. A significant change can be interpreted as an increase of 0.5 points or more in the mean score of a subscale. Thus, increases in the mean scores of the preparation, action, and maintenance stages are considered indicative of progress in motivation toward the adoption and consolidation of regular physical exercise. Conversely, high scores on the precontemplation subscales reflect low readiness for change or resistance to modifying sedentary behavior. The internal consistency of this questionnaire shows Cronbach’s Alpha values>0.70 for each of the factors resulting from the factor analysis: precontemplation (0.71), contemplation (0.71), preparation (0.75), action (0.71) and maintenance (0.70) [43].

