**Design and methodology:**

Quasi-experimental controlled study, single-center, parallel, two-branch, with a 12-month follow-up. We plan to recruit up to a total of 169 participants, who will be assigned in a 1:1 ratio to a control group (who will receive e-mails) and an intervention group (who will receive face-to-face group and individual visits and telephone calls). The active intervention has a duration of 6 months and will be carried out by nursing professionals. The primary outcomes are sedentary time measured with the Sedentary Behavior Questionnaire (SBQ) and the use of accelerometers, and the state of motivation to change measured through the Transtheoretical Model of Physical Exercise Change Questionnaire (TMPECQ).

**Trial registration.** ClinicalTrials.gov (NCT06893146).

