Recent studies in adults with type 2 diabetes show that interrupting prolonged periods of sitting with light activity, such as walking at low intensity for 3 minutes every half hour for 8 hours, reduces postprandial glucose, insulin, C-peptide, and triglyceride levels [14]. Replacing sitting time with standing (2.5 hours per day) and walking at low intensity (totaling 2 hours and 20 minutes per day) every 30 minutes improves 24-hour blood glucose levels and insulin sensitivity more than structures physical exercise [15]. Stair climbing has also been shown to be effective in lowering postprandial glucose levels [16,17], although it does not have a positive impact on glycosylated hemoglobin (HbA1c) [18]. A study of young people with obesity and glucose intolerance showed that 5-minute pause intervals every hour for 12 hours were more effective in reducing blood glucose levels than 1 hour of moderate-intensity exercise at the beginning of the day [19]. Another study indicated that short but intense exercise times (6 x 1-minute brisk walk at 90% of maximum heart rate) 30 minutes before main meals improved glycemic control in people with diabetes more than a single 30-minute session of moderate-intensity walking [20]. In general, any reduction in sitting time has been shown to be beneficial for people with type 2 diabetes [21].

This shows that, in addition to exercise, reducing sedentary lifestyle has a significant impact on the health and glycemic control of people of all ages with this condition. It is essential to promote programs that modify the lifestyle of the population, addressing the adoption and long-term maintenance of habits that reduce sedentary time. In addition to increasing physical activity, it is considered necessary to implement strategies to reduce sedentary behavior. This may be a more agile objective, serving as a complementary strategy to improve both physical fitness and metabolic health in individuals with type 2 diabetes.

In this regard, the novelty of the design lies in the structured integration of educational and motivational components with a specific focus on reducing sedentary behavior, developed and implemented from nursing practice, with both in-person and telephone follow-up. This approach enables personalized, sustainable, and adaptable care within real healthcare settings, with the potential to improve adherence and quality of life in individuals with type 2 diabetes.

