### Objectives

The general objective of the study is to know the effect of decreasing sedentary time and increasing motivation to adopt an active lifestyle of different health-related parameters in patients diagnosed with type 2 diabetes mellitus. Also to provide support and resources for the proper management of diabetes. Likewise, it will be verified that face-to-face interventions and telephone interventions by nursing professionals decrease the sedentary time in the diabetic population and if it means and improvement in clinical, anthropometric and biochemical parameters. Also, to evaluate the quality of life and the degree of motivation aimed at reducing sedentary time and to integrate the reduction of sedentary time in the lifestyle of the participants with practical tools and guidelines adapted to the circumstances.

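### The primary motivation outcome measures readiness for physical exercise, so it cannot support conclusions about motivation to reduce sedentary time

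*Protocol article*

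**What the plan says.** The Abstract (Design and methodology) names two kinds of primary outcome in one sentence. It begins "The primary outcomes are sedentary time measured with the Sedentary Behavior Questionnaire (SBQ) and the use of accelerometers" and adds "the state of motivation to change measured through the Transtheoretical Model of Physical Exercise Change Questionnaire (TMPECQ". No other motivation instrument is described.

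The section on the state of motivation to change describes the TMPECQ in exercise terms. It places a person in a stage of change "regarding his or her willingness to engage in physical exercise". One set of items gives reasons for not exercising, and "these items should only be completed by participants who do not exercise regularly"; a parallel set gives reasons for exercising regularly. Rises in the preparation, action and maintenance scores are taken as "indicative of progress in motivation toward the adoption and consolidation of regular physical exercise". The section Clinical characteristics likewise lists the variable as motivation concerning physical exercise, separately from sedentary lifestyle.

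Two places tie the outcome to sitting instead. The Objectives section includes the aim to evaluate "the degree of motivation aimed at reducing sedentary time". The measurement section says that high precontemplation scores "reflect low readiness for change or resistance to modifying sedentary behavior".

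**The concern.** The intervention described under Study design focuses on reducing sedentary time, and one stated objective is motivation for that behaviour. The instrument asks about a different behaviour. The protocol's own rationale depends on the difference: the Introduction argues that long sitting does harm even in people who meet exercise guidance, that standing and slow walking can replace it, and that "In addition to increasing physical activity, it is considered necessary to implement strategies to reduce sedentary behavior".

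At stake is what the trial may conclude from one of its primary outcomes. If the objective and the precontemplation sentence are followed as written, a null TMPECQ result can be reported as failure to motivate people to sit less, and a positive one as success. Neither follows from a score for exercise readiness. The label also travels: the Statistical analysis section compares groups on level of motivation to change and plans exploratory subgroups by it.

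**Working it through.** No arithmetic applies. The protocol gives no figure that links exercise readiness to motivation to sit less, so the check sets the statements side by side.

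1. **What the instrument measures.** Its stated aim, the content of its items, the routing of respondents and the meaning of progress all refer to exercise. Respondents are routed by whether they exercise regularly, not by how long they sit.

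2. **What the objectives ask.** There are two motivation targets. The general one (Abstract and Objectives) is motivation towards an active lifestyle. The specific one, later in Objectives, is "the degree of motivation aimed at reducing sedentary time". Exercise readiness covers part of the first. Nothing in the instrument as described addresses the second.

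3. **What would justify the link.** Evidence would be needed that the exercise stages track readiness to sit less. The figures attached to the instrument are Cronbach's alphas (precontemplation 0.71, contemplation 0.71, preparation 0.75, action 0.71, maintenance 0.70), a mean of 4 or more for strong identification with a stage, and a rise of 0.5 points for a significant change. Alpha shows that the items of a subscale agree with each other. It does not show that they measure a construct they do not ask about. The Statistical analysis section adds only a general remark that the motivation questionnaire (under another abbreviation, which I take to be the same instrument) has been evaluated psychometrically.

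4. **Whether the protocol treats the two behaviours as one.** It does not. The Introduction presents sitting as a hazard independent of exercise and its reduction as a complementary strategy. The precontemplation sentence conflicts with that.

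5. **Where the readings part.** Cross the two motivations, each changed or unchanged:

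| Motivation to sit less | Exercise readiness | What TMPECQ reflects | Read as motivation to sit less |
|---|---|---|---|
| changed | changed | change | agrees |
| unchanged | unchanged | no change | agrees |
| changed | unchanged | no change | wrong |
| unchanged | changed | change | wrong |

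The two discordant rows are possible on the protocol's own account of the behaviours. Their frequency is not given and cannot be derived, so the discrepancy cannot be sized. Its direction is not fixed either: the third row understates and the fourth overstates motivation to sit less.

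6. **What is not affected.** Sedentary time is measured directly by the Sedentary Behavior Questionnaire and accelerometer at each time point, independently of the TMPECQ.

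**The case against.** The strongest reply is that the protocol is open about its construct. The questionnaire has physical exercise in its name, the Clinical characteristics section labels it that way, and progress is defined in exercise terms. The headline objective is an active lifestyle, and the sitting-specific aim is a later, subsidiary clause. The intervention is also a lifestyle programme whose first session covers healthier habits generally, so movement in exercise readiness is a plausible effect. Only one sentence in the measurement section crosses from exercise to sitting, and it also offers the neutral reading of low readiness for change.

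Most of this stands, and it narrows the point. The TMPECQ is a relevant outcome and a partial measure of the general objective. What remains is that the subsidiary aim is a stated objective with no measure of its own, and that the crossing sentence supplies the reading a report could use to claim one.

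A reader might infer three stronger things:

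- **That a successful intervention could be missed.** It would not be missed on this account: a fall in sedentary time is captured by the other primary outcome. Only a change in motivation could be misjudged.
- **That people who sit less without wanting to exercise will score as resistant, or that regular exercisers have no room to improve.** The items are in an appendix that is not shown, and no baseline score distribution is given, so neither can be asserted.
- **That a definite share of the motivational effect is lost.** Any such share would be invented. Nor would the fraction of people who change sitting alone bound the loss, because effects on two different scales need not be equal per person.

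**Conclusion.** The point holds as a mismatch between a primary outcome, one stated objective and one interpretive sentence. The TMPECQ measures stage of change for physical exercise. It is a partial proxy for motivation towards an active lifestyle and not a measure of motivation to reduce sedentary time. Reading high precontemplation as resistance to changing sedentary behaviour is unsupported by the instrument as described and conflicts with the Introduction.

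The consequence is limited to conclusions about motivation, positive or null; the evaluation of sedentary time stands. No size can be given. The verdict assumes that the article's description of the questionnaire is faithful to its items. If the appendix contained items about sitting, the description would need correcting instead. The matter should be settled before results are interpreted, because it decides what one primary outcome can be said to show.

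**What to change.** Three wording changes suffice:

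1. Name the primary outcome, and the corresponding clause in Objectives, as stage of change (readiness) for physical exercise measured by the TMPECQ. Use the same name in the Statistical analysis section, including the subgroup variable.
2. Delete the part of the precontemplation sentence that refers to sedentary behaviour.
3. State that conclusions on motivation are limited to exercise readiness, and that conclusions on sitting rest on the Sedentary Behavior Questionnaire and accelerometer.

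This costs no data collection and no change to the analysis. The price is giving up a claim about motivation to sit less.

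Optionally, if the team wants to keep that objective, it could add a staging item worded for reducing or breaking up sitting time at T0 to T3, as an exploratory measure. The item is brief but unvalidated, which should be stated, and it can show change from baseline only if it is in place before the T0 measurements. Whether to add it is a matter of judgement; the wording changes do not depend on it.

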#### Physical activity level.

To measure the level of physical activity, the short, self-administered format of the “International Physical Activity Questionnaire” (IPAQ) (S6 Appendix) will be used. Questions are asked about the time spent in activity in the last 7 days, with a distinction between vigorous activity, walking and sitting. The results are calculated in terms of minutes per week, multiplying the number of days by the duration of the activity in minutes, obtaining a value in minutes per week for each of the categories. A person is considered inactive when he/she does not reach the recommended threshold of moderate physical activity (150 minutes per week), sufficiently active if he/she reaches 150 minutes of moderate activity or 75 minutes of vigorous activity per week and very active if he/she exceeds 300 minutes of moderate activity or 150 minutes of vigorous activity per week recommended by the WHO. The correlation coefficient of the short version of the questionnaire is 0.76 [44].

#### Quality of life in people with diabetes.

The validated Spanish version of the Diabetes Quality of Life Questionnaire (DQoL) (S7 Appendix) will be used. It is a tool that measures quality of life in people with diabetes. Participants rate the items on a 5-point Likert-type scale, in which 1 reflects total disagreement and 5 reflects total agreement), other items are rated from 1 (very satisfied) to 5 (very dissatisfied). The results of the scores are quantified, a higher score indicates a better quality of life, while a lower score suggests a greater negative impact of diabetes on the patient’s life. The internal consistency of this questionnaire shows Cronbach’s alpha values of 0.68 to 0.86 [45].

### Statistical analysis

First, a descriptive analysis of the sociodemographic, clinical and anthropometric data of the participants will be performed. Quantitative variables (such as age, BMI, glucose, cholesterol and blood pressure levels) will be described using means ± standard deviation (for those with normal distribution) and medians (with 25^th^ and 75^th^ percentiles) when they do not follow a normal distribution. Qualitative variables (such as sex, educational level, and marital status) will be described as relative frequencies, cumulative relative frequencies, and percentages. These analyses will be performed using Microsoft Excel for data organization and IBM SPSS Statistics for statistical calculations.

The normality of quantitative variables will be assessed using normality tests, such as the Shapiro-Wilk or Kolmogorov-Smirnov tests, as appropriate. To evaluate the homogeneity of variances and sphericity in repeated measures, Mauchly’s test will be applied. To evaluate the efficacy of the intervention, the two groups of the study will be compared: CG and IG at different times (T0, T1, T2, T3). For continuous variables, a repeated measures analysis of variance (repeated measures ANOVA) will be conducted, applied only if the assumptions of residual normality and sphericity are met. In case of violation of the sphericity assumption, Greenhouse-Geisser or Huynh-Feldt corrections will be used to adjust the degrees of freedom. If the variables do not meet the normality assumption or the distribution is clearly non-parametric, the non-parametric Friedman test will be employed to analyze differences between repeated measurements.

The chi-square test will be applied to compare the distribution of qualitive variables between the two groups, such as the presence of comorbidities or the level of motivation to change. To establish statistical significance, a significance level of p < 0.05 will be used.

Regarding the handling of missing data, a descriptive analysis will be conducted to identify its pattern and proportion. An intention-to-treat (ITT) analysis will be adopted, including all participants assigned regardless of their adherence or losses during follow-up. For quantitative variables with missing data, multiple imputation will be applied using the Multiple Imputation by Chained Equations (MICE) method, generating several complete datasets that will be analyzed to improve accuracy and reduce bias. Additionally, a sensitivity analysis will be performed comparing results from imputed and complete data to assess the robustness of the conclusions.

One of the objectives of the study is to evaluate how the reduction of sedentary time is related to improvements in clinical parameters such as glucose, lipid and blood pressure levels. To this end, Pearson correlations will be used to analyze the relationship between sedentary time (measured with accelerometers) and changes in these parameters. In addition, multiple linear regression models will be used to adjust the analyses for possible covariates (age, sex, antidiabetic treatment, etc.).

Subgroup analyses based on relevant participant characteristics (such as age, sex, and level of motivation to change) will be considered exploratory and conducted with the aim of identifying possible differences in response to the intervention. To control for multiplicity across primary and secondary outcomes, the Bonferroni correction will be applied to adjust the significance level and minimize false positives. Given the relatively small number of comparisons, this conservative approach is appropriate and unlikely to substantially reduce statistical power. Results from these analyses will be interpreted with caution.

Changes in quality of life and motivation to change will be analyzed using the corresponding validated questionnaires. Both will be analyzed using repeated measures analysis of variance or linear regression to determine whether the interventions have a positive impact on these aspects over time.

The reliability and validity of the instruments used, such as the SBQ and the ActiTrainer accelerometer, have been verified. These instruments will measure sedentary lifestyle in an objective and reliable manner. On the other hand, the internal validity of the MTCEJ and DQOL Questionnaire has also been evaluated by psychometric analysis.

The results of the statistical analysis will be presented in tables and graphs to facilitate interpretation of the data, accompanied by confidence intervals to estimate the magnitude of the observed effects. Finally, the results will be discussed in relation to the existing literature on sedentary lifestyles in people with type 2 diabetes and the effectiveness of similar interventions.

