### Measurements and evaluations

Data will be collected at baseline (T0), three months (T1), interim (6 months = T2) and 12 months (T3) from the start of the study.

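### No primary time point or deciding between-group contrast is named for any primary outcome, and the Bonferroni rule covers outcomes but not visits or ANOVA terms

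*Protocol article*

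**What the plan says.** All locations are in the protocol article.

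- **Primary outcomes** (Abstract, Design and methodology): "The primary outcomes are sedentary time measured with the Sedentary Behavior Questionnaire (SBQ) and the use of accelerometers", together with motivation to change measured by the TMPECQ. No time point is attached to any of them.
- **Visits:** "Data will be collected at baseline (T0), three months (T1), interim (6 months = T2) and 12 months (T3) from the start of the study" (in Measurements and evaluations). The visits are not ranked.
- **Treatment period** (Abstract, Design and methodology): "The active intervention has a duration of 6 months". Follow-up lasts 12 months, so T2 falls at the end of active treatment and T3 six months later.
- **Efficacy analysis** (Statistical analysis): "the two groups of the study will be compared: CG and IG at different times (T0, T1, T2, T3"). The method is given as "For continuous variables, a repeated measures analysis of variance (repeated measures ANOVA) will be conducted", and "a significance level of p < 0.05 will be used".
- **Motivation and quality of life** (Statistical analysis): repeated measures ANOVA or linear regression, "to determine whether the interventions have a positive impact on these aspects over time". Motivation level is also listed for a chi-square comparison of the groups, with no visit given.
- **Multiplicity** (Statistical analysis): "To control for multiplicity across primary and secondary outcomes, the Bonferroni correction will be applied". Visits and model terms within an outcome are not mentioned.
- **Masking** (Group allocation and masking): the principal investigator collects and analyses the data, and outcome assessors are not blinded.

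**The concern.** A two-group, four-visit repeated measures ANOVA yields tests of group, time and group × time, and invites up to three post-baseline group comparisons. These tests answer different questions:

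- The group term averages in T0, before any intervention effect can exist.
- The group × time term says that the profiles differ, but not when or in which direction.
- T2 asks whether the intervention works by the time it ends. T3 asks whether any benefit lasts six months beyond that.

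The efficacy sentence lists all four visits, including baseline, on an equal footing, so the article does not say which result would count as success on a primary outcome. Allocation is sequential and unconcealed, and an unblinded investigator both collects and analyses the data. A rule fixed in advance is therefore one of the few safeguards against choosing the favourable visit or term after seeing the results.

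**Working it through.** **Inputs from the article.** 169 participants (84 CG, 85 IG), 15% dropout, four visits, significance level 0.05 (taken as two-sided).

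**Assumptions, because the article gives no figures.** Between-visit correlation 0.5 (range 0.3 to 0.85), effects in SD units, and a Bonferroni divisor of 3 (SBQ, accelerometer, TMPECQ).

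**1. The plan's own sample size.** The finite-population formula for a proportion, with N = 230, e = 0.05, z = 1.96 and p = 0.5 (assumed), is n = N·z²·p(1−p) / [e²(N−1) + z²·p(1−p)] = 144.1. Then 144.1/0.85 = 169.5, against 169 stated, so the figure reproduces. About 144/2 = 72 per arm remain after dropout.

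**2. False positives at 0.05 if any candidate test may decide.** If the tests were independent:

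- two ANOVA terms: 1 − 0.95² = 9.75%
- three post-baseline visits: 1 − 0.95³ = 14.3%

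The tests are not all independent, so the no-effect case was simulated. There were 20,000 trials per setting, with 84/85 and 72/72 per arm, compound-symmetric and AR(1) correlation, and a Greenhouse-Geisser corrected interaction.

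| What may decide | False-positive rate per outcome | Multiple of 5% |
|---|---|---|
| One named ANOVA term (group, or group × time) | 4.5–5.4% | about 1 |
| Group or group × time | 9.2–9.9% | 1.8–2.0 |
| Any of T1, T2, T3 | 9.3–14.0% | 1.9–2.8 |

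At compound-symmetric correlation 0.5, either term gives about 10% and any visit about 12–13%.

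**3. The same with Bonferroni over three primary measures.** The level per test is 0.05/3 = 1.67%. Under independence:

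- two terms: 1 − (1 − 0.0167)² = 3.3%
- three visits: 1 − (1 − 0.0167)³ = 4.9%

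Simulation (72 per arm, compound symmetry, 60,000 trials per correlation) gives 3.2–3.3% for either term. For any visit it gives 3.3–4.6%, and 4.5% at correlation 0.5. The multiples at correlation 0.5 are 3.2/1.67 = 1.9 and 4.5/1.67 = 2.7. Bonferroni lowers the level but leaves the proportional inflation.

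**4. Does the choice change the answer?** Assume a fading effect of 0.25, 0.5 and 0.1 SD at T1, T2 and T3, with 72 per arm, correlation 0.5, level 0.05 and unadjusted visit contrasts. The standard error of a visit contrast is √(2/72) = 0.167 SD.

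- T2: z = 0.5/0.167 = 3.0, power 85%
- T3: z = 0.1/0.167 = 0.6, power 9%
- Group term: mean effect (0 + 0.25 + 0.5 + 0.1)/4 = 0.2125 SD. Its standard error is √(0.625 × 2/72) = 0.132, so z = 1.6; simulated power is 35%.
- Group × time: simulated power 76%

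In the same simulated data sets, T2 and T3 disagree on significance in 77% of trials, and the group and group × time terms in 57%. With a constant 0.4 SD effect after baseline, the two terms still disagree in 46%.

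**The case against.** **The 10–14% figures ignore the plan's Bonferroni correction.** This stands as to level. No outcome would be tested at 0.05 if the correction is applied as written, and a divisor above 3 (secondary outcomes are included) would lower the rates further. It does not remove the inflation relative to whatever level is used.

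**The inflation needs a pick-the-winner rule that the protocol does not state.** This also stands. The figures are conditional on that behaviour; they describe what the wording permits, not what the authors intend.

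**A reader might infer that a time effect would be taken as efficacy**, from "to determine whether the interventions have a positive impact on these aspects over time". The article does not support this. That sentence concerns quality of life and motivation only, and the Statistical analysis section defines efficacy as a comparison of CG with IG. A clarifying sentence is still worthwhile, because the limitations paragraph concedes that season may influence sedentary behavior.

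**A reader might infer that leaving the contrast open costs power.** This is not shown in general. With 0.2/0.4/0.1 SD at T1/T2/T3, a baseline-adjusted T2 contrast has about 77% power against about 53% for the interaction. An unadjusted T2 contrast has about 66%, so part of the gap comes from covariate adjustment, and the assumed profile peaks at T2. With a constant 0.4 SD effect and no adjustment, a single visit (67%) does no better than the interaction (68%).

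**Significant at T2 and not at T3 is not a contradiction.** That is fair: these are different questions, and confidence intervals are promised. The gap is that the article does not say which question is primary.

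**A condensed article may leave this to the analysis plan.** Post hoc adjustment and similar detail may indeed sit there. The time point, however, is part of what defines a primary outcome, and the article does state the efficacy comparison, with baseline included among the visits compared.

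**Conclusion.** The point holds in limited form and should be fixed. The article names no primary time point and no deciding between-group contrast for any primary outcome, and its multiplicity rule does not reach visits or ANOVA terms.

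If any significant visit or term may be claimed as success, the false-positive rate per outcome is roughly 2 to 2.8 times nominal. The multiple depends on the assumed between-visit correlation, and the absolute rate also on the Bonferroni divisor, which the article does not state. The disagreement rates depend further on assumed effect profiles. That the candidate tests can disagree does not depend on fading, since it also occurs under a constant effect.

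The text does not settle which visit should be primary. The 6-month active period points to T2. The labels intermediate and interim for T2, and the 12-month follow-up, point to T3.

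**What to change.** In the Statistical analysis section:

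1. Name one deciding IG minus CG contrast for each primary outcome, estimated from the longitudinal model, with the T0 value as baseline and not as an efficacy visit.
2. Choose T2 (end of the 6-month active intervention) or T3 (end of the 12-month follow-up) for that contrast. The choice is the authors' and should be fixed before outcome data are examined.
3. Test the other of these two visits only if the first is significant, and report T1 as supportive.
4. State that a time effect common to both groups is not evidence of efficacy.

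The Bonferroni correction can then be applied across outcomes as planned, with one deciding test per primary outcome. The change costs a few sentences and needs no new data. The small downside is that an effect seen only at the non-primary visit could not be claimed as the primary result.
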